## Abstract

**Introduction:**

The increasing burden of mental distress reported by healthcare professionals is a matter of serious concern and there is a growing recognition of the role of the workplace in creating this problem. Magnet hospitals, a model shown to attract and retain staff in US research, creates positive work environments that aim to support the well-being of healthcare professionals.

**Methods and analysis:**

Magnet4Europe is a cluster randomised controlled trial, with wait list controls, designed to evaluate the effects of organisational redesign, based on the Magnet model, on nurses’ and physicians’ well-being in general acute care hospitals, using a multicomponent implementation strategy. The study will be conducted in more than 60 general acute care hospitals in Belgium, England, Germany, Ireland, Norway and Sweden. The primary outcome is burnout among nurses and physicians, assessed in longitudinal surveys of nurses and physicians at participating hospitals. Additional data will be collected from them on perceived work environments, patient safety and patient quality of care and will be triangulated with data from medical records, including case mix-adjusted in-hospital mortality. The process of implementation will be evaluated using qualitative data from focus group and key informant interviews.

**Ethics and dissemination:**

This study was approved by the Ethics Committee Research UZ/KU Leuven, Belgium; additionally, ethics approval is obtained in all other participating countries either through a central or decentral authority. Findings will be disseminated at conferences, through peer-reviewed manuscripts and via social media.

**Trial registration number:**

ISRCTN10196901.

Strengths and limitations of this studyMagnet4Europe uses a cluster randomised controlled trial design with wait list controls in over 60 hospitals in six European countries.A multicomponent strategy is used to support implementation of a complex intervention at the hospital level, aimed to improve clinician well-being.The Magnet4Europe intervention is tailored to European hospitals, facilitating implementation and transferability without disrupting clinical practice.Contextual factors such as different health systems within and across countries may impact the standardised Magnet4Europe intervention and unintentionally lead to variation in the intervention and outcomes.Embedding a complex intervention at hospital-level takes time and any effect might become apparent only after the study ends.

## Introduction

Mental health and well-being are high priorities for the European Union (EU).^1^ Mental health conditions account for 22% of the EU’s disease burden measured in Years Lived with Disability, thus imposing a significant burden on individuals, society and the economy.^2^ Health workers experience greater levels of job-related burnout and other mental health disorders than those in other sectors.^3 4^ An earlier European study of working conditions in European hospitals, identified high rates of job dissatisfaction and burnout, with burnout rates among nurses varying from 10% to 78%^5 6^ while the corresponding figures from studies of physicians ranged from 25% to 60%, varying among organisations and medical specialties.^7–10^ Burnout in the healthcare workforce not only impacts on those experiencing it, leading to depression, substance abuse and even suicide^11–15^ but is also associated with worse patient outcomes, lower patient satisfaction,^6^ medical errors,^16^ reduced quality and safety^17^ and reduced efficiency of hospitals.^18^ The resulting lost productivity, combined with current recruitment challenges, further threatens the already overstretched health workforce, widening the gap between provision of health services and population needs.^19^

This situation has been exacerbated by the COVID-19 pandemic,^20^ increasing anxiety and stress among clinicians^21^ and further impacting on health workers’ mental health.^22–24^

Effective, affordable and sustainable interventions to improve health professionals’ mental health and well-being are essential if we are to interrupt the vicious cycle of high burnout, worsening mental health, lost productivity and unsafe care.^25^ Interventions to prevent burnout can be divided into two types: first, psychological interventions aimed at individual level and second workplace redesign. There is only limited evidence of the impact of individual psychological approaches to improve resilience and coping skills (eg, mindfulness).^26^ The second approach, redesigning the organisational environment in which health professionals provide care, aims to reduce modifiable sources of clinician stress and burnout, reinforce clinicians’ perceptions of well-being and enhance their autonomy and control over the conditions of their work. There is substantial research pointing to organisational redesign as the most promising of these two approaches.^27^

The finding that the causes underlying burnout in nurses and physicians are similar and, especially, are rooted within the work environment^28–31^ provides a compelling rationale for prioritising the redesign of hospital environments to address this issue. In the 1980s, hospitals in the USA were faced with high nurse turnover,^32 33^ low retention, and increasing early retirement rates.^34^ Despite the general nursing shortage, some US hospitals—later referred to as Magnet hospitals—were more successful in recruiting and retaining nurses by creating a positive work environment. Features characterising these hospitals included flat decentralised organisational structures, empowering frontline staff in decision-making and transformational leadership.^35^ The original characteristics of these hospitals^36^ were developed into 14 forces of Magnetism and later configured into 5 components of the Magnet model that was used to establish the criteria for Magnet designation.^37^ A robust body of evidence, primarily stemming from US hospitals, documents the association of the Magnet model with improved well-being of staff, including lower burnout, higher job satisfaction, lower intent to leave their job,^38 39^ in addition to positive financial outcomes for organisations,^40 41^ higher levels of patient satisfaction^42 43^ and improved clinical outcomes.^44 45^ Longitudinal panel studies have found that hospitals that follow the Magnet model improve their work environments, well-being of staff and patient outcomes, compared to other hospitals. Two international pilots tested the transferability of the Magnet model, demonstrating the feasibility of achieving positive results outside the USA. One, in England, focused primarily on the implementation of the Magnet process.^46^ The other, a four-hospital intervention with accompanying evaluation in Russia and Armenia, used the Magnet model with twinning with Magnet recognised hospitals.^47^ In both cases, the intervention hospitals improved their work environments substantially from their baselines within the 2-year intervention and achieved better outcomes for staff, such as reduced dissatisfaction, intent to leave and emotional exhaustion (EE), while perceived quality of care improved. Despite the large body of evidence and recent uptake in two European hospitals, Magnet organisational redesign initiatives have not been adopted widely in Europe.

The aim of the Magnet4Europe project is to evaluate the ability of organisational redesign in European hospitals to improve nurses’ and physicians’ mental health and well-being. The organisational redesign intended in Magnet4Europe is a system-level intervention, targeting the hospital as a whole on the level of the organisation. Through co-creation and stakeholder co-designed adaptations, the Magnet model is adapted to the European context, providing the first element and basis for the Magnet4Europe intervention. In addition to this first component, one-to-one twinning with Magnet recognised hospitals, learning collaboratives and a critical mass of hospitals are also introduced into the intervention. While the Magnet4Europe intervention shares common elements with other organisational interventions, the combination of all the above components, targeting two major clinical professions—both nurses and physicians—and its primary focus on the work environment as levers for change differentiate the Magnet4Europe intervention from any other organisational intervention and make it unique in its kind.^48^

## Methods and analysis

### Study design and setting

Magnet4Europe will use a usual-practice cluster randomised controlled trial with wait list controls in a nested mixed-methods evaluation. The study protocol for this study follows ‘the Standard protocol items: recommendations for intervention trials 2013 statement’ (SPIRIT, online supplemental file 1).^49^ The setting will be acute general hospitals in six European countries, including both EU member states (Belgium, Germany, Ireland and Sweden) and non-EU member states (England and Norway). These six countries also represent two dominant types of health systems, ie, Bismarck and Beveridge,^50^ that vary with regards to the extent of national government intervention in health services delivery, something that may be a factor in uptake of innovation.

10.1136/bmjopen-2021-059159.supp1Supplementary data

### Eligibility

European hospitals are eligible to participate if: (1) no Magnet designation by the American Nursing Credentialing Centre (ANCC) had been acquired in the past or at the time of the start of the intervention, (2) bed size ≥150 and (3) the hospital is focused on acute care for adults, including wards in the area of internal medicine and/or surgery. Excluded are highly specialised hospitals, for example, psychiatric hospitals, tropical medicine or paediatrics.

Within each hospital, registered nurses and physicians (including residents) will be eligible to participate in the quantitative and qualitative evaluation of the intervention if they: (1) have direct patient contact, (2) meet the minimum qualifications as stipulated by Directive 2013/55/EU amending Directive 2005/36/EC on the recognition of professional qualifications and (3) work on adult inpatient units including intensive care units and the emergency room. Nurses and physicians working in specialised units such as neonatology, paediatrics, obstetrics, psychiatry, operating room, pathology, microbiology, radiology and medical imaging will be excluded.

### Study sample

A two-phased non-probability strategy will be used to sample organisations at the hospital level. First, in February and March 2019, principal investigators in the six European countries contacted eligible hospitals (see below) within those countries to consider taking part in the study using various recruitment strategies. Hospitals were informed of the Magnet4Europe objectives and methodology and were invited to show their interest in participating by submitting a letter of intent by March 2019. In spring 2020, participating hospitals (some of the original expression of interest sites and other new ones) were asked to confirm their commitment by signing an agreement committing to participate for the full duration of the study period and adhere to the Magnet4Europe protocol.

Sample size will be determined based on the power calculation for a cluster randomised controlled trial with before-and-after measures.^51^ The calculated design effect is based on average cluster size and the intraclass correlation coefficient (ICC), a measure of the amount of dependency among observations within classes (ie, hospitals in our study).^51 52^ Power calculation will be performed for the primary outcome of interest, burnout, measured by the EE subscale of the Maslach Burnout Inventory (MBI).^53^ The estimated prevalence rate of EE is 30% based on the team’s earlier RN4CAST study.^6^ In order to detect a 20% relative reduction (ie, a 6 percentage point reduction) in burnout with a power of 80% and an alpha of 5%, an average cluster size of 200 and an ICC of 0.025,^54^ this study will require 10 253 health professionals in 51 clusters per measurement occasion (at endpoint of the study).

Based on the power calculation, we aim to include 60 general acute care hospitals in six countries (Belgium, England, Germany, Ireland, Norway and Sweden) and recruit at least 200 professionals per hospital.

### Randomisation

Randomisation to intervention and control group is at the hospital level. Within each country, hospitals will be matched on three characteristics, (1) bed size, (2) teaching status and (3) high technology, using a Euclidian distance matrix based on the smallest within pair covariate distance. Subsequently, simple random sampling—allowing for selection with equal probability—will be used to allocate one hospital within each matched pair of hospitals to the immediate intervention group or the wait list control group. Both immediate intervention group and wait list controls will be informed which group they have been allocated to. Given the characteristics of the intervention in which active participation of the hospitals is required, blinding to the intervention will not be possible.

### Intervention

A multicomponent intervention comprising organisational redesign of hospitals will be implemented in both arms of the study. The intervention was launched in the immediate intervention group in month 10 of the project (October 2020) and will have a total duration of 31 months. The intervention in the usual-practice wait list control group will be initiated in month 17 (May 2021) and will last for 24 months (figure 1).

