The second intervention component consists of one-to-one twinning between European hospitals aspiring to implement the Magnet model and longstanding US Magnet designated hospitals. This seeks to promote capacity building through transfer of knowledge, skills, tools, technologies and best practices, thereby supporting positive reciprocal organisational changes.^55^ An equal number of US Magnet hospitals—recognised for having an excellent work environment—will be recruited; allowing for a 1:1 twinning ratio of European intervention hospitals with US Magnet Hospitals. The twinning pairs will meet every two weeks virtually and two face-to-face mentoring sessions are planned each year when travel is safe. Face-to-face meetings between both parties allow for a profound, impact- and meaningful experience that maximises the effect of the capacity building activities facilitating the intended organizational redesign.

Third, learning collaboratives will take place throughout the duration of the project and will be accessed and attended by all European hospitals in which the intervention is taking place at that point in time. The learning collaboratives will also involve policymakers, so as to promote sustainability. Learning collaboratives build on the concept of communities of practice,^56^ involving people coming together to engage in a process of learning in a shared domain of interest. These will be held monthly using remote means of communication with the possibility of in-person meetings annually when travel is safe. Effective elements of collaboratives, that is, learning sessions, action periods and a collaborative extranet, will be implemented.^57–59^

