### Quantitative evaluation

#### Quantitative data collection

Quantitative data collection across countries is standardised using an online data collection platform. Quantitative survey data will be collected at three points in time, that is, at baseline (T0) in months 11–12 of the project timeline, at T1 (months 28–29) and T2 (months 41–42) (figure 1) during an 8 week period. An open cohort design will be employed in which all eligible nurses and physicians are invited to participate in each of these three measurement points (T0–T2). Nurses and physicians will be recruited within each hospital at baseline and will be asked to participate in surveys with repeated measures taken over the three points in time allowing partially longitudinal follow-up of a cohort of individuals. Initial non-participants and new employees will be invited to join the study at later measurement points. Regular reminders will be sent to any clinicians (registered on the platform) through the online data collection platform who have not or only partially completed the survey. Individual informed consent for participation will be obtained by the researchers at the first contact (online supplemental file 2). Each record of informed consent is retained on the online platform.

10.1136/bmjopen-2021-059159.supp2Supplementary data

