#### Data analysis

Regression models to estimate the association between the intervention and outcomes will include fixed effects of time, intervention and intervention by time. Hospitals represent higher order units of analysis, and clinicians the lower order unit of analysis. Countries will be treated as fixed effects. Repeated measures on nurses and physicians will also be appropriately modelled. More complex multilevel structural models will be employed to examine indirect and moderated associations between the process measures which we would expect to respond to the intervention and our outcome measures. All analyses will be conducted according to intention-to-treat. Data on hospital characteristics (eg, size, teaching status) and clinicians (eg, gender, age) will be collected and used to adjust for potential confounders in the regression analyses. Statistical significance will be assessed at the 5% level. Occasional missing data will be limited by the electronic survey implementation using a force response option for each item. Data analysis will be conducted using SAS software, V.9.4 (and subsequent releases) of the SAS system for windows (SAS Institute, Cary, North Carolina).

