The research activities conducted within the project are expected to improve significantly the work environment of health professionals in hospitals, especially after the COVID-19 pandemic. In particular, Magnet4Europe proposes an organisational intervention, targeting the root of many of the problems (ie, organisational and work-related stressors) facing health systems rather than focusing narrowly of their symptoms. It does so by means of a multicentre study involving more than 60 hospitals across six European countries. By choosing a cluster randomised controlled design, this study is the first with the power to identify a causal association between implementing healthy workplace characteristics and improved staff well-being in European hospitals on a large scale. Two international pilot initiatives testing the transferability of Magnet key principles and accompanied by rigorous evaluations have informed the design of Magnet4Europe.^46 47^ In both, the intervention hospitals improved their work environments substantially from their baselines at the end of the 2-year intervention, and outcomes for staff improved. The Magnet4Europe intervention builds on lessons learnt from these pilot initiatives. The degree of innovation can also be seen in the use of a multifaceted implementation strategy involving one-to-one twinning with international Magnetdesignated hospitals, creation of a critical mass, co-creation of solutions, development of learning collaboratives, benchmarking and interdisciplinary and management buy-in. In addition, Magnet4Europe makes a strong scientific contribution as it goes beyond traditional studies, which focus solely on individual professions and disciplines separately. This allows us to study the interaction between physicians and nurses working in teams and the impact of healthy environments on their well-being and patient outcomes.

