Despite having a strong conceptual design for the Magnet4Europe study, that is, a cluster randomised controlled trial, bearing many advantages and having the potential to facilitate the robust evaluation of this type of intervention, this design is susceptible to multiple sources for potential risk of bias. First, contamination of the wait list control group cannot be ruled out. All hospitals were, prior to the start of the intervention, informed about the intervention and the active components. It was not possible to blind hospitals to their allocation in either the immediate intervention group or wait list control group. We aimed to mitigate contamination of hospitals assigned to the wait list control group by not providing them with the Magnet blueprint of organisational redesign and by not disclosing the name of their future Magnet twinning partner to avoid early contact and exchange of information prior to their actual start of the intervention. A second additional risk related to contamination is when the intervention takes longer to be fully embedded as intended. The intervention proposed in Magnet4Europe is a complex intervention at the hospital level, earlier research findings demonstrated that a considerable amount of time is required for the intervention to become fully embedded into practice and influence outcomes accordingly. Due to the limited time frame available in Magnet4Europe, no transition period is incorporated. This potential risk is mitigated by two intervention components, that is, the one-to-one twinning of the European intervention hospitals with a designated and experienced US Magnet hospital and the Learning Collaboratives. Both components are expected to act as a catalysator for knowledge transfer and innovation and expedite the implementation of the intervention. There is a potential risk that the true effect of the intervention only becomes apparent after the formal ending of the 4-year study period. A longer follow-up of the study beyond the funding is foreseen.

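### Both arms are on the intervention before either follow-up survey, so the stated 80% power does not apply to intervention versus usual practice at T1 or T2

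*Protocol article*

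**What the plan says.** The Study design and setting section describes a usual-practice cluster randomised trial with wait-list controls. The Intervention section starts the immediate arm in month 10, for 31 months. Of the other arm it says: "The intervention in the usual-practice wait list control group will be initiated in month 17 (May 2021) and will last for 24 months".

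The Quantitative data collection section puts the baseline survey (T0) in months 11–12 and the follow-ups "at T1 (months 28–29) and T2 (months 41–42").

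The Study sample section sizes the trial for a fall in emotional exhaustion from 30% to 24%, with 80% power, 5% alpha, clusters of 200 and an ICC of 0.025. The result is 10 253 "health professionals in 51 clusters per measurement occasion (at endpoint of the study"). The target is then set at 60 hospitals.

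Under Data analysis, the models "will include fixed effects of time, intervention and intervention by time". The Discussion claims that "this study is the first with the power to identify a causal association between implementing healthy workplace characteristics and improved staff well-being".

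**The concern.** A sample size for 30% versus 24% at the endpoint needs a control arm that is still at the untreated rate at that time. On the protocol's own timetable there is no such arm at T1 or T2. The only survey with a usual-practice comparator is T0, and it falls 1–2 months after the immediate arm's launch, so it is not a clean baseline in that arm either.

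What is at stake is how the result is read. If the intervention works, and works about as well after 24 months as after 31, the arms will look alike at T2. A reader who trusts the 80% figure would take that as evidence of no effect. The remaining evidence would be change within arms from a late-2020 baseline, which randomisation does not protect from time trends.

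**Working it through.** **Reproducing the plan's figure.** Inputs from Study sample: 30% versus 24%, 80% power, 5% alpha (two-sided assumed, as sidedness is not stated), cluster size 200, ICC 0.025.

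- n per arm = [1.96·√(2·0.27·0.73) + 0.84·√(0.30·0.70 + 0.24·0.76)]² / 0.06² = 858.3
- Design effect = 1 + 199·0.025 = 5.975
- Total = 2·858·5.975 = 10 253; divided by 200, this is 51.3 clusters

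The figure reproduces. At 60 hospitals of 200, the effective size is 6000/5.975 = 1004 per arm, and power for 6 points is 86%.

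**Exposure at each survey.** Starts are months 10 and 17. At T2 exposure is capped at the stated durations of 31 and 24 months.

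| Survey | Immediate arm | Wait-list arm |
|---|---|---|
| T0, months 11–12 | 1–2 months | 0 |
| T1, months 28–29 | 18–19 | 11–12 |
| T2, months 41–42 | 31 | 24 |

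**Contrast and power.** The documents give no effect-over-time curve, so the curves below are assumptions. Each reaches the planned 6 points. An arm's rate is 30% minus the effect at its exposure. Power is two-sided, with 1004 effective observations per arm, and each survey is treated as a cross-section, as the plan's sample size does.

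Example, linear over 24 months, T1 at month 28:

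- wait list 30 − 6·11/24 = 27.25%; immediate 30 − 6·18/24 = 25.50%; difference 1.75 points
- standard error √(2·0.264·0.736/1004) = 1.97 points, so 1.75/1.97 = 0.89
- power = Φ(0.89 − 1.96) + Φ(−0.89 − 1.96) = 14%

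| Assumed build-up to 6 points | T1 difference (power) | T2 difference (power) |
|---|---|---|
| Linear over 12 months, then flat | 0–0.5 (5–6%) | 0 (5%) |
| Linear over 18 months, then flat | 2.0–2.3 (18–23%) | 0 (5%) |
| Linear over 24 months, then flat | 1.75 (14%) | 0 (5%) |
| Linear over 31 months | 1.35 (10%) | 1.35 (11%) |
| None for 12 months, then linear to 24 | 3.0–3.5 (32–41%) | 0 (5%) |
| None for 12 months, then linear to 31 | 1.9–2.2 (15–19%) | 2.2 (21%) |
| Step: none at 12 months, all at 18 | 6 (86%) | 0 (5%) |
| Step: none at 24 months, all by 31 | 0 (5%) | 6 (86%) |

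Where the difference is 0, the 5% is the type I error rate. Ranges at T1 run over its two survey months.

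**The case against.** The design is open about delayed treatment of controls. The Intervention section says both arms receive the programme, and the Limitations section warns that the effect may appear only after the study ends. That stands, but the Limitations section treats contamination only up to the control arm's own start. It does not say that the control arm is treated at both follow-ups, or what that does to power.

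The size of the loss depends on a curve that the documents do not supply. This also stands. The Limitations section describes slow embedding, so lagged curves belong in the range, and they are the more favourable ones (up to 41% at T1 and 21% at T2). Baseline adjustment or the matching could add precision, but the documents give no correlation from which to say how much.

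Some stronger readings are tempting and are not supported:

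- **That a null arm contrast is the most likely result.** The pilot hospitals "improved their work environments substantially from their baselines within the 2-year intervention", which makes a small contrast at T2 plausible. It does not show that the effect is complete by 24 months.
- **That shared learning collaboratives let the wait list catch up.** The sessions "will be accessed and attended by all European hospitals in which the intervention is taking place at that point in time", but nothing states how this changes the pace of uptake.
- **That the planned extension is offered as a remedy.** The text says only that "A longer follow-up of the study beyond the funding is foreseen". It does not claim to restore an untreated comparator, and with both arms treated it would not.
- **That T1 should move to months 15–16, before the wait list starts.** Exposure would be 5–6 versus 0 months. Under the linear curves over 18, 24 and 31 months the contrast would be 1.7–2.0, 1.25–1.5 and 1.0–1.2 points, no larger than at the existing T1. Under a 12-month lag it would be 0. Only the 12-month curve favours the move (2.5–3.0 points).

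**Conclusion.** Wrong as written. The timing follows from the protocol's dates alone: no follow-up survey has a usual-practice control, and the randomised comparison at T1 and T2 is early versus 7-months-delayed start. The sample-size arithmetic is correct. What fails is its premise of an untreated 30% control rate at the endpoint. It would go too far to say that the trial has no power, because a step effect inside the 7-month gap would keep 80%, though at one survey only. Under the gradual curves tried, power is about 5–41% at T1 and 5–21% at T2. Those ranges rest on a full effect of 6 points, 60 hospitals of 200, the plan's ICC and the assumed curves. The model with time, intervention and their interaction compares two treated arms and cannot restore the missing comparator.

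**What to change.** 1. Reconcile Study sample, Intervention and Quantitative data collection. Replace the 80% statement with the power for early versus 7-months-delayed start at each follow-up, over stated build-up assumptions that include lagged ones.
2. Define the randomised estimand at T1 and T2 as early versus delayed start, and drop the usual-practice label for those waves. State that a null arm contrast there does not show the intervention to be ineffective, and that before-after change within an arm is not randomised evidence. Qualify the causal-power claim in the Discussion to match.

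As supporting analysis, the team may consider T1 as the primary time point, and an exposure-time model that allows for lag and plateau. A purely linear months-since-start term would not fit an effect that levels off.

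The cost is a change of wording and, if chosen, one further model; no new data are needed. The downside is a stated power much less favourable than 80%.
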